**TREATMENT PROTOCOL**

- 1. **Patient monitoring – upon arrival at NICU/ICU**
- Place continuous SaPO2 monitor
- Insert indwelling urinary catheter to monitor urine output
- Insert gastric tube to avoid gastric retention, and for administration of Salovum® and placebo.
- Insert arterial catheter for arterial mean pressure monitoring – MAP should be zeroed at the level of Foramen Monroe.
- Monitor pupil size and reactivity to light each hour
- New CT scan if clinically motivated
- Insert intracranial pressure monitoring device – intra-parenchymal or intraventricular. Intraventricular monitors should be zeroed at the level of the foramen of Monroe.
  1. **General measures**
- Head and neck in neutral position and aligned
- Avoid hyperthermia - Defined as central temperature ≥ 38 ° C
  - - - - Paracetamol
- Early enteral nutritional support
  - - - - Before 48 hours
        - 15-20 Kcal/kg weight
- Pharmacologic prophylaxis if post traumatic seizures
  - - - - Drug according to local praxis
- Gastric bleeding prophylaxis
  - - - - Drug according to local praxis
- Avoid deep venous thrombosis
  - - - - Proceed according to local praxis
- Frequent tracheal suctioning with sterile technique to prevent pulmonary infections
  1. **Respiration**
- Mechanical ventilation.
  - - - - Ventilate patient to normal PaCO2 (4,6 – 5,2 kPa), normal PaO2 (12-14 kPa) PEEP ≈ 5 cm H2O, and intermittent bagging to prevent atelectasis.
- Hyperventilation – PaCO2 between 4,0 – 4,5, only as a temporary measure to cope with an ICP-crisis according to local practice.
  1. **Fluids**
- According to local praxis
  1. **Pharmacology**
- According to local praxis
- Use of Pentothal will be noted in protocol
  1. **Administration of Salovum® or Placebo**
- All patients enrolled in protocol must have a gastric feeding tube.
- Administration of Salovum® or placebo - 1 g per patient weight in kg per 24 hours divided into 6 administrations, dissolved in 50-100 ml of water per administration.
- Treatment will be given for 5 days/120 hours = 30 administrations, or until the ICP monitor is removed.

1. **STUDY MEASUREMENTS AND ENDPOINTS**

In this study the following data will be measured/recorded in a patient specific folder, clearly marked with the patient study number. Data will later be transferred to an excel sheet for statistical analysis. The excel sheet will only contain study number. Data that can be used to identify the study participants will be stored in a locked cabinet in the study site.

- 1. **Medical history/demographics**

The occurrence of diabetes and antithrombotic therapy prior to present trauma will be noted in addition to MRN, Date of birth, gender and address.

- 1. **Details pertaining the trauma**

Trauma mechanism will be noted. Time elapsed from trauma to assessment by neurosurgeon. Pupil status will be recorded at screening, when assessed by neurosurgeon.

- 1. **Physiological and clinical data**

Patient ICP and Mean Arterial Blood Pressure (MAP) will be recorded at screening/inclusion and on an hourly basis.

Patient GCS will be recorded at screening/inclusion. Neurointensive care specific treatment will be registered as TIL (Treatment Intensity Level) every 24 hours. The TIL scale used will be the differentiated TIL scale with a score ranging from 0-38 (Appendix 3).

All clinical data will be recorded for as long as the patient is treated in the neurosurgical ICU.

Gastro paresis will be evaluated every 4 hours by aspirating via the patients´ nasogastric tube, prior to administration of Salovum®/Placebo. Gastro paresis will be evaluated during the entire treatment time (see 4.6)

- 1. **Blood samples**

Once the patient is included in the trial, blood will be drawn and sent for centrifugation of plasma and storage in a -80°C freezer. Additionally, a blood sample will be drawn 2-3 days into treatment and after last dosage of trial substance. The plasma will be analyzed for AF levels, markers of brain damage and cytokines/chemokines for exploratory ad-hoc studies.

- 1. **Primary end point**

Mortality at 30 days

- 1. **Secondary end points**

TIL – Treatment Intensity Level

Intracranial pressure (ICP)

1. **ADVERSE EVENTS**

An adverse event (AE) is the development of disadvantageous medical symptoms or conditions, or deterioration of a pre-existing medical condition, that occur as the result of participating in the study.

As Salovum® is commercially available in Swedish pharmacies and has been available for human use for many years without any reported toxicity, it is not expected to cause any adverse events. Allergy to egg yolk protein (Gal 5; alpha-livetin) has an estimated low incidence in adults (< 0.1 %) and anaphylactic reactions are very rare among these. However, special care will be taken to ensure that no vital parameters are changed for the worse in conjunction with the start-up of administering the drug/placebo, and at the time for each dose administration, i.e. every 4 hours.

The physician responsible for the patient will assess if any Adverse or Serious Adverse Events have occurred during the course of each day. The daily patient chart states: “Do you consider that there is a reasonable possibility that an adverse event has been caused by the study compound administered?” The question must be answered daily.

Adverse events:

Skin rash and hives.

Serious adverse events

Serious anaphylactic reaction with hypotension and bronchospasm requiring intervention with corticosteroids and/or vasopressors.

1. **STATISTICAL METHODS**

**Mortality at 30 days**

The power of the proposed end points was calculated with R statistical software using the Fisher test (1) and power t-test (2 and 3) acknowledging the fact that there are no adequate power tests for skewed data.

*Mortality*. Reduction of rate of mortality from 40% (20/50 patients) to 16% (8/50 patients) after intervention will give a p=0.01, odds ratio=0.29, 95% confidence interval=0.10-0.80.

*Treatment intensity level*. Proposed reduction by 5 grades (delta) after intervention with n=50 in intervention and control group gives power 0.80 with sd=7.19.

*Intracranial pressure (ICP)*. Reduction of ICP after intervention. Proposed reduction by 5 mm Hg (delta) or 5 hours over 20 mm Hg after intervention with n=50 in intervention and control group each gives a power of 0.80 with standard deviation (sd)=7.19

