AF is commercially available as Salovum®^®^ and is a product based on egg yolk powder B221^®^ as the source for AF. It is available in pharmacies without prescription. Salovum®^®^ is classified as a “medical food” by the European Union (see Appendix 1. Salovum®^®^ is currently registered in the Republic of South Africa.

- 1. **Study Rationale**

To this date, no efficient treatments exist against traumatic cerebral edema. AF has been shown to counteract edema caused by other pathologies in humans. Animal experiments have proven AF to reduce traumatic cerebral edema and reduce development of focal hemorrhagic contusions.

Since 1,5 years, AF has been given to adult patients with severe traumatic brain injury in the Department of Neurosurgery, Lund University Hospital, Sweden. Our preliminary findings suggest that in at least 3 out of 5 patients, AF has had an effect in reducing ICP and thereby avoiding decompressive hemicraniectomy. The study has been granted ethical permission (see Appendix 2). Salovum® has been a classified as a food supplement by the local ethics committee and the Swedish Pharmaceutical Agency (see Appendix 2)

Though, the number of patients with severe traumatic head injury in Sweden is decreasing and the need for a larger, randomized trial in a centre with large volumes of traumatic brain injury is needed

To evaluate if AF can be beneficial for patients in this group, we plan to perform a prospective, randomized double-blinded, placebo-controlled trial.

1. **STUDY OBJECTIVES**

The primary objective of this study is to evaluate the effect of the protein Antisecretory factor (AF), given as a dietary supplement to adult patients with severe traumatic brain injury. We will assess 30-day mortality, ICP, and treatment intensity level (TIL, see Appendix 3) for this purpose.

1. **STUDY PLAN AND PROCEDURES**
   1. **Study status**

After approval by the ethics committee, recruitment started in September 2017. Expected end date is June 2021. The trial was registered at [www.clinicaltrials.gov](http://www.clinicaltrials.gov) with NCT03339505 on September 17, 2017. The study is expected to be completed by June 2021.

- 1. **Study design**

The study is prospective, double-blinded, placebo-controlled, and interventional.

Primary outcome for this study will be 30-day mortality.

Secondary outcomes will be ICP and TIL (Treatment Intensity Level).

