The study population will be adult patients (18-65 years) that are treated in the NICU for severe traumatic brain injury. Recruitment will be via the patients´ next of kin, who will be asked about participation in the study. Recruitment will continue until 100 patients have been randomized into the 2 groups (active substance and placebo) of 50 patients each. If no next of kin can be found, the patient can be included in the study according to paragraph 30 Helsinki Declaration (see also 3.7.2).

- 1. **Inclusion criteria**

To be enrolled, the following criteria have to be fulfilled:

1. Adult of either gender between 18 and 65 years.
2. Non-penetrating, isolated severe traumatic brain injury
3. GCS >3 and GCS<9 on admission or within 48 hours after injury*
4. Admission to study hospital within 24 hours of injury*
5. No known history of allergy to egg-protein
6. Planned for intracranial pressure monitoring
7. Absence of bilaterally dilated pupils
8. CT scan with traumatic pathology that is more than an isolated epidural hematoma

*Within 24 hours of injury (for patients with GCS < 9 on admission) or

Within 24 hours of deterioration (among patients deteriorating to GCS < 9 within 48 hours of injury)

- 1. **Exclusion criteria**

Any of the following is regarded as a criterion for exclusion from the study:

1. No consent
2. Systolic blood pressure below 90 mm Hg post resuscitation
3. Non-fulfillment of inclusion criteria after screening and inclusion procedures.

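### The one mortality method the protocol names, an unadjusted Fisher test, has about 71% power at its own 40% vs 16%; a prespecified analysis using recorded baseline data would do better with the same 100 patients

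*Protocol*

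**What the plan says.** Study design in the protocol fixes the primary endpoint: "Primary outcome for this study will be 30-day mortality". The sample size is given under Study population: "Recruitment will continue until 100 patients have been randomized into the 2 groups (active substance and placebo) of 50 patients each".

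In Statistical Methods, under Mortality at 30 days, the planning basis is stated as "The power of the proposed end points was calculated with R statistical software using the Fisher test (1"), where the number in brackets appears to mark mortality as the first of three endpoints. The effect assumed is a "Reduction of rate of mortality from 40% (20/50 patients) to 16% (8/50 patients) after intervention", and the result attached to it is "p=0.01, odds ratio=0.29, 95% confidence interval=0.10-0.80". No power and no alpha are given for mortality, although a power of 0.80 is quoted for both secondary endpoints.

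The protocol also collects baseline prognostic data. Details pertaining the trauma says "Pupil status will be recorded at screening, when assessed by neurosurgeon". Physiological and clinical data says "Patient GCS will be recorded at screening/inclusion". Date of birth is recorded under Medical history/demographics, so age is known. Randomisation is by numbered packages, 50 per arm, and neither Randomization procedure nor section 8.2.1 describes strata.

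**The concern.** Fisher's test conditions on the total number of deaths. With 50 per arm the attainable p-values are coarse, so the test rejects less often than its nominal level allows, and that costs power. The method as named also makes no use of age, GCS or pupil status, and nothing in the described allocation balances them.

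The figures given for mortality do not reveal this. They show what a single hypothetical table would yield, and they do not show how often a trial of this size would reach significance. At stake is the chance of detecting the planned effect on the primary endpoint with about 50 × 0.40 + 50 × 0.16 = 28 expected deaths.

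**Working it through.** **Inputs.** From the protocol: 50 per arm, 40% (20/50) vs 16% (8/50), Fisher's test. Assumed: two-sided alpha of 0.05, which is not stated but fits the reported "95% confidence interval=0.10-0.80". Also assumed: the joint AUC of age, GCS and pupil status for 30-day death, which the protocol does not give. It is varied from 0.60 to 0.79.

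**1. The protocol's own figure.** Fisher's exact test on 8/50 vs 20/50:
- sample odds ratio (8 × 30)/(42 × 20) = 240/840 = 0.286; conditional maximum-likelihood estimate 0.289
- exact 95% CI 0.097 to 0.797
- p = 0.0135

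This reproduces the stated result.

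**2. True error of Fisher's test.** Sum over all 51 × 51 tables with i and j deaths:

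size(p) = Σ C(50,i) C(50,j) p^(i+j) (1−p)^(100−i−j), over tables with Fisher p ≤ 0.05.

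| Common death rate | 16% | 28% | 40% | 50% |
|---|---|---|---|---|
| Fisher | 2.5% | 3.1% | 3.2% | 3.5% |
| Uncorrected chi-square | 5.5% | 5.0% | 5.2% | 5.7% |

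**3. Power of unadjusted tests at 40% vs 16%.** Same enumeration, with separate rates in the two binomial terms:
- Fisher 71.3%
- Boschloo 75.1%, maximum error 4.87%
- uncorrected chi-square 77.9%

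Changing only the unadjusted test therefore recovers 75.1 − 71.3 = 3.8 points with error strictly held, or 77.9 − 71.3 = 6.6 points with a test that can slightly exceed 5%.

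**4. Cross-check by sample size.** With mean rate 0.28 and difference 0.24, 80% power needs

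n = [1.960 √(2 × 0.28 × 0.72) + 0.842 √(0.40 × 0.60 + 0.16 × 0.84)]² / 0.24² = (1.2445 + 0.5150)² / 0.0576 = 53.7, so 54 per arm.

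The continuity correction, which approximates Fisher, gives (53.7/4) × [1 + √(1 + 4/(53.7 × 0.24))]² ≈ 61.8, so 62 per arm. Fifty is short on either count.

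**5. Adjusted analysis.** Simulation of 6,000 trials of 50 + 50, with marginal risks held at 40% and 16%. The model is logistic regression on arm plus three baseline covariates, tested by Wald. One set used three normal covariates (AUC 0.63, 0.70, 0.74, 0.79). The other used age uniform on 18-65, GCS uniform on 4-8 and 20% pupil abnormality (AUC 0.60, 0.65, 0.70, 0.77). These distributions are assumptions.

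| Assumed AUC | Wald power | Over Fisher (71.3%) | Over chi-square (77.9%) |
|---|---|---|---|
| 0.60 | 77.4% | +6.1 | −0.5 |
| 0.63 | 78.7% | +7.4 | +0.8 |
| 0.65 | 79.6% | +8.3 | +1.7 |
| 0.70 | 80.5-81.1% | +9.2 to +9.8 | +2.6 to +3.2 |
| 0.74 | 82.4% | +11.1 | +4.5 |
| 0.77 | 83.8% | +12.5 | +5.9 |
| 0.79 | 85.2% | +13.9 | +7.3 |

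The simulation standard error is about √(0.8 × 0.2/6000) = 0.5 points. Under a common 28% death rate, the Wald test's error was 4.8-5.3% across these settings and the likelihood-ratio test's was 5.4-6.0%, which favours Wald. Power of a Firth-penalised fit was not computed.

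**6. Sensitivity to the effect measure.** If the conditional odds ratio is held at 0.286 and the marginal risks are not, both powers fall and the gap widens: 68.2% vs 75.9% at AUC 0.63, 63.3% vs 73.8% at 0.70, and 50.9% vs 68.1% at 0.78. The active-arm risk then rises to about 17-20%, so this is no longer the protocol's own scenario.

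**The case against.** The strongest objection is that the sentence on Fisher's test describes a power calculation. A reader might infer that the protocol commits the trial to an unadjusted Fisher test as its final analysis. It does not say so. Publications & Contributions refers to a statistical analysis plan, which is not at hand and may already specify adjustment. The absence of a covariate model would not be a finding by itself. This stands, and it limits the point to the planning basis that the protocol does state.

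A reader might also infer a loss of 10 points or more. That requires a joint AUC of roughly 0.70 or higher. The documents give no AUC, and eligibility (GCS 4-8, age 18-65, no bilaterally dilated pupils) narrows the prognostic spread.

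Nor do the figures show that baseline severity is the main source of noise. At AUC 0.70 the covariates add only about 3 points over an unadjusted chi-square test, and most of the gain there comes from leaving Fisher.

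Finally, Fisher's test is valid: it keeps error below 5%, and that error rate already allows for chance imbalance under randomisation. The issue is efficiency. An adjusted model has its own costs, namely a conditional odds ratio and about 28/4 = 7 deaths per parameter (arm plus three covariates).

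**Conclusion.** The point holds as one of efficiency in the named planning basis. Fisher's power of about 71% and true error of about 3% follow from the protocol's own rates and sample size, given a two-sided 5% level. Boschloo's 75% needs no covariate assumption. The adjusted figure of roughly 77-85%, a gain of about 6-14 points, depends on an assumed AUC of 0.60-0.79 and on marginal risks of 40% and 16%. Up to about 7 of those points come from Fisher's conservatism alone.

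The documents do not support saying that the final analysis is fixed as unadjusted, that the trial's error is uncontrolled, or that the loss is at least 10 points. Extending the argument to ICP would also go beyond what was checked. The change is worth making because it needs no new data and no more patients.

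**What to change.** Before unblinding, and ideally before the unblinded interim analysis at 95 patients, state in Statistical Methods that the primary mortality analysis is a logistic regression of 30-day death on arm, adjusted for age, GCS at inclusion and pupil status, with a Wald or Firth-penalised test chosen in advance. Report a standardised risk difference beside the conditional odds ratio. Keep an unadjusted comparison as a sensitivity analysis, with Boschloo's test in place of Fisher's. If the analysis plan already does this, align the protocol with it.

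The cost is an amendment of wording. The downsides are an odds ratio that is conditional on the covariates, hence the risk difference, and about 7 deaths per model parameter, which is a reason to keep to these three covariates and to consider penalisation.

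### The power statement for 30-day mortality is the p-value of one imagined result; actual power for 40% vs 16% is about 0.71 if alpha is two-sided 0.05, and about 0.47 at 0.01

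*Protocol*

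**What the plan says.** The protocol makes mortality the primary endpoint (Study design): "Primary outcome for this study will be 30-day mortality". Under Study population it fixes the size: "Recruitment will continue until 100 patients have been randomized into the 2 groups (active substance and placebo) of 50 patients each".

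The sizing statement is in Statistical methods, under the mortality heading. It opens: "The power of the proposed end points was calculated with R statistical software using the Fisher test (1) and power t-test (2 and 3". The numbering matches the three endpoints listed there: mortality, TIL and ICP.

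- **Mortality:** "Reduction of rate of mortality from 40% (20/50 patients) to 16% (8/50 patients) after intervention will give a p=0.01, odds ratio=0.29", followed by "95% confidence interval=0.10-0.80". No power is given.
- **TIL:** "Proposed reduction by 5 grades (delta) after intervention with n=50 in intervention and control group gives power 0.80 with sd=7.19".
- **ICP:** the same difference of 5, the same standard deviation and the same power of 0.80.

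No significance level and no sidedness are stated for any of the three.

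**The concern.** Power is the probability of a significant result over all the outcomes that could occur if the assumed rates are true. The mortality sentence instead takes the assumed rates as if they were the observed counts, exactly 20 and 8 deaths, and reports the test on that one table. Sampling variation, which power exists to measure, is left out. The primary endpoint is thus the only one of the three without a power, although the section says that power was calculated for all of them.

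Two things are at stake. First, this is the only quantitative support in the protocol for 50 per arm on the primary endpoint, and it does not show how likely the trial is to detect the effect it assumes. Second, the missing alpha matters because the figures in the section do not all point to the same level. The 95% interval suggests 0.05, while the TIL and ICP figures fit 0.01.

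**Working it through.** **Inputs.** From Statistical methods: control mortality 0.40 (20/50), treated mortality 0.16 (8/50), Fisher's exact test; for TIL and ICP, difference 5, standard deviation 7.19, n = 50 per arm, power 0.80. From Study population: 50 per arm. Alpha and sidedness are not stated, so the result is shown at several levels.

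**Step 1: reproduce the stated mortality figures.** Fisher's test on 8 deaths and 42 survivors against 20 deaths and 30 survivors:

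| Quantity | Protocol | Recomputed |
|---|---|---|
| Two-sided p | 0.01 | 0.0135 |
| Odds ratio (conditional) | 0.29 | 0.289 |
| 95% CI (exact conditional) | 0.10 to 0.80 | 0.097 to 0.797 |

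All three match, so the printed numbers are the output of one test on one table.

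**Step 2: actual power.** Let X be the control deaths, binomial(50, 0.40), and Y the treated deaths, binomial(50, 0.16). Then

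power = Σ Pr(X = x) × Pr(Y = y), summed over all of the 51 × 51 tables whose Fisher p-value is at or below alpha.

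| Method, n = 50 per arm, 40% vs 16% | Power |
|---|---|
| Fisher, two-sided 0.05 | 0.713 |
| Fisher, two-sided 0.01 | 0.467 |
| Fisher, one-sided 0.05 | 0.802 |
| Continuity-corrected normal, two-sided 0.05 | 0.694 |
| Pooled normal, two-sided 0.05 | 0.770 |
| Pearson chi-square, exact enumeration, two-sided 0.05 | 0.779 |
| Arcsine, two-sided 0.05 | 0.780 |
| Unpooled normal, two-sided 0.05 | 0.792 |

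No two-sided method tried reaches 0.80. With the protocol's own test at two-sided 0.05, the chance of missing a true fall from 40% to 16% is 1 − 0.713 = 0.287.

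As a sensitivity check (the 20% is the reviewer's value, not the protocol's), Fisher power at two-sided 0.05 for 40% vs 20% is 0.515.

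**Step 3: which alpha do the other two lines imply?** For a two-sample t-test with n = 50 per arm:

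- noncentrality = (5 / 7.19) × √(50/2) = 0.6954 × 5 = 3.477, with 98 degrees of freedom
- two-sided 0.05: critical t = 1.984, power = 0.931
- two-sided 0.01: critical t = 2.627, power = 0.800

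Solving for the standard deviation that gives power 0.80 yields 7.191 at alpha 0.01 and 8.836 at alpha 0.05. The printed 7.19 therefore matches 0.01 to the last digit.

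**Step 4: put the two together.** At alpha 0.01 the illustrated mortality result, p = 0.0135, exceeds alpha and would not be significant; rounding it to 0.01 hides this. With 20 control deaths, seven treated deaths would be needed (p = 0.0063). At alpha 0.05 the illustrated result is significant, and up to 10 treated deaths would be (p = 0.049; 11 gives p = 0.083).

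**The case against.** The strongest reply is that the protocol never claims 80% power, or any power, for mortality, and that its arithmetic is right. Both are true. The fault is that the quantity reported is not the one the section says was calculated.

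The next objection is that 0.71 rests on an alpha the protocol does not give. This stands. Two-sided 0.05 is an assumption supported by the 95% interval and convention; one-sided 0.05 would give 0.80, though nothing in the protocol points to one-sided testing; 0.01 would give 0.47. The 0.01 is itself inferred from the TIL and ICP figures and is not stated. So 0.71 may be quoted only with its condition attached.

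A reader might also infer that 50 per arm was derived from the mortality figure. The protocol does not say so: it evaluates n = 50 for three endpoints without naming the one that set it. Nor does it say that a non-significant result will be read as no effect on mortality. That is a prediction about readers, and how such a result will be interpreted may be covered in the analysis plan, which is not shown.

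Finally, the Interim analysis section allows the sample size to be increased. The figures above ignore that option. It does not repair the power statement: the look comes when 95 of the 100 patients are included, and the protocol gives no rule for the increase.

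**Conclusion.** The point holds: the mortality sentence is wrong as a power statement, and nothing else in the protocol supplies the missing figure. Power for 40% vs 16% with 50 per arm and Fisher's exact test is about 0.71 at two-sided 0.05 (assumed) and about 0.47 at two-sided 0.01, the level at which the TIL and ICP lines reproduce. At 0.05 those two lines would have power 0.93, not 0.80. The section cannot be read consistently until one alpha is stated.

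These values assume the protocol's own rates, 30-day status known for all 100 patients, and the fixed design before any interim increase. The documents do not support a stronger reading, namely that the trial has an unconditional power of 0.71 or that its size was derived from the p-value.

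**What to change.** 1. State one significance level and its sidedness for the whole section.
2. Replace the mortality sentence with the actual power at that level. If two-sided 0.05 is chosen: *With 50 patients per arm and a two-sided alpha of 0.05, Fisher's exact test has about 71% power to detect 30-day mortality of 40% vs 16%.* Adding 52% for 40% vs 20% as a sensitivity figure is optional. If two-sided 0.01 is chosen, the figure for 40% vs 16% is about 47%.
3. Restate the TIL and ICP power on the same alpha: 0.93 at two-sided 0.05, or 0.80 at two-sided 0.01, for a difference of 5 and a standard deviation of 7.19.
4. Say that the figures are for the fixed design of 100 patients, before any sample-size increase at the interim analysis.

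The cost is a wording change in the protocol and a less favourable statement for the primary endpoint. No extra patients, data or change of test are requested.

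### The protocol gives the ICP secondary endpoint two alternative scales joined by *or*, with one SD for both and no common observation window

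*Protocol*

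**What the plan says.** The Study design section and the list of secondary end points name the endpoint only as ICP, without a summary measure or a period. The ICP paragraph of Statistical Methods is the only place that gives it a scale, and it gives two: "Proposed reduction by 5 mm Hg (delta) or 5 hours over 20 mm Hg after intervention". The sentence continues that "n=50 in intervention and control group each gives a power of 0.80 with standard deviation (sd)=7.19". The treatment intensity level (TIL) paragraph uses the same numbers: "Proposed reduction by 5 grades (delta) after intervention with n=50 in intervention and control group gives power 0.80 with sd=7.19".

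On data collection, Physiological and clinical data says "Patient ICP and Mean Arterial Blood Pressure (MAP) will be recorded at screening/inclusion and on an hourly basis" and "All clinical data will be recorded for as long as the patient is treated in the neurosurgical ICU". The section on administration of the study product says "Treatment will be given for 5 days/120 hours = 30 administrations, or until the ICP monitor is removed". The protocol sets no common window for ICP. It does not relate hours above 20 mm Hg to hours monitored, and it does not say how death or removal of the monitor enters the endpoint.

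The same Statistical Methods section plans for mortality of 40% in the control arm and 16% in the intervention arm. Study Objectives lists ICP among the three measures for the primary objective. The Interim analysis section has the data monitoring committee review both primary and secondary outcomes before it recommends stopping for futility, continuing, or enlarging the trial.

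**The concern.** There are two linked problems.

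First, the endpoint is not a single variable. A change in pressure and a change in time spent above a threshold can disagree in size, in significance and even in direction. With *or* between them, either could be reported as the planned ICP result.

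Second, the hours version is sensitive to observation time if it is analysed as a plain count. A patient cannot contribute more hours above 20 mm Hg than were recorded. A patient who dies at 30 hours contributes at most 30. A survivor can contribute 120 or more. The trial is planned around a large survival difference, so monitored time would be expected to differ between arms to the extent that deaths fall within the monitored period. A treatment that saves lives would then accumulate more hours at risk, and its ICP result would be pulled towards no effect or beyond. Because the interim review takes in secondary outcomes, the measure could influence more than a secondary table.

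**Working it through.** **1. The plan's own figure.** Inputs from Statistical Methods: difference 5, SD 7.19, 50 per arm, t-test, power 0.80. The section states neither alpha nor sidedness. Standardised difference: 5 / 7.19 = 0.695. Two-sample t-test power (noncentral t) at 50 per arm:

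- two-sided alpha 0.05: 0.931
- two-sided alpha 0.025: 0.883
- two-sided alpha 0.01: 0.800

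Of the settings tried, only two-sided 0.01 returns the stated 0.80. At two-sided 0.05, about 34 per arm would give it. The same 5 and 7.19 stand for mm Hg, hours and TIL grades, so 7.19 cannot be read as the spread of hours in particular.

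**2. Dependence of a plain count on monitored time.** Mortality is from the protocol (0.40 and 0.16). Everything else is an assumption: survivors are monitored for 120 h and spend p = 10% of hours above 20 mm Hg; every death falls within 120 h; patients who die are monitored for m hours on average and spend a share q of those hours above 20 mm Hg.

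Expected count in an arm with mortality d: (1 − d) × 120p + d × q × m.

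Difference, active minus control: (0.40 − 0.16) × (120p − qm) = 0.24 × (12 − qm).

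Mean monitored time at m = 60: control 0.60 × 120 + 0.40 × 60 = 96.0 h; active 0.84 × 120 + 0.16 × 60 = 110.4 h.

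| m (monitoring of deaths, uniform) | q | Control, h | Active, h | Active − control, h |
|---|---|---|---|---|
| 60 (24–96 h) | 10% | 9.60 | 11.04 | +1.44 |
| 72 (24–120 h) | 10% | 10.08 | 11.23 | +1.15 |
| 42 (12–72 h) | 10% | 8.88 | 10.75 | +1.87 |
| 60 | 35% | 15.60 | 13.44 | −2.16 |
| 72 | 35% | 17.28 | 14.11 | −3.17 |
| 42 | 35% | 13.08 | 12.43 | −0.65 |

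With equal burden there is no ICP difference to find, yet the count puts the active arm 1.15 to 1.87 h worse. That is 23% to 37% of the 5-hour target, in the wrong direction.

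With q = 35%, the mean share of monitored hours is 0.60 × 10 + 0.40 × 35 = 20% in control and 0.84 × 10 + 0.16 × 35 = 14% in active. The 6-point gap equals 7.2 h per 120 h. The count shows 0.65 to 3.17 h of it. The direction is right but the size is reduced.

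**3. Where the direction changes.** The sign turns when qm = 12, that is at q = 12 / m: 20% for m = 60, 16.7% for m = 72 and 28.6% for m = 42.

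**4. Later deaths.** If only a share s of deaths in each arm falls within the window, the hours lost from the comparison are 0.24 × s × q × (120 − m). At m = 60:

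- s = 1: 1.44 h (q = 10%) or 5.04 h (q = 35%; this is 7.20 − 2.16)
- s = 0.5: 0.72 h or 2.52 h
- s = 0: none

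Early monitor removal in survivors would narrow the difference in monitored time. Recording beyond 120 h would widen it.

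**The case against.** The sentence with the two scales is a power assumption and does not define an endpoint. The protocol does not say that hours will be totalled without regard to monitored time, and it does not say when the measure will be chosen. Its section on publications and contributions mentions a statistical analysis plan, which is not shown and may set the summary measure, the window and the handling of death. This stands in part: the missing death rule alone would not be a finding. But this sentence is the only text that gives ICP a scale, and it offers two alternatives under one SD. That is something the protocol states badly, whatever a later document adds.

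A reader might infer that early death or monitor removal counts as a better ICP result. The documents do not support that as a general statement, for four reasons.

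- It could apply only to an unnormalised hours count. An average in mm Hg over available hours is not lowered automatically by death.
- Even for the count, a dying patient with 35% of 60 hours above 20 mm Hg contributes 21 h, against 12 h for a survivor, so death still counts as worse.
- The mortality figures are for 30 days, and no passage places the deaths within the first five.
- The monitor-removal clause ends treatment; the recording period is set by ICU stay. If a monitor is removed because pressure is controlled, the unrecorded hours are probably low and add little to a count.

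Giving deaths the worst rank is also open to objection as a main analysis. It brings the primary endpoint into ICP, so that a mortality difference alone could produce an apparent ICP effect.

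**Conclusion.** The point holds in limited form. The protocol leaves ICP with two unreconciled scales and a single SD of 7.19 without a unit, and nothing in it prevents the choice being made after the data are seen. It would go too far to say that this is intended, or that the analysis plan leaves it open as well.

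The exposure problem is conditional on a plain hours count. Under the planned mortality it would weaken a true ICP benefit. It would reverse the benefit only if dying patients had a burden close to that of survivors, below about 20% of hours in the base case. The figures of +1.15 to +1.87 h with equal burden, and of 0.65 to 3.17 h seen out of 7.2 h, rest on assumed burdens, on 120 h of monitoring in survivors and on all deaths falling within the window. They shrink in proportion as deaths fall later. They show that the effect can be material against a 5-hour target; they do not estimate it. For a secondary endpoint this should be corrected, and it does not bear on the primary analysis of mortality.

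**What to change.** Delete *or* and name one ICP endpoint. A workable choice is the percentage of monitored hours with ICP above 20 mm Hg during hours 0 to 120 from first dose, with mean ICP over the same window as supportive.

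State how death and monitor removal within the window are handled. A percentage does not settle this by itself, since removal after pressure is controlled leaves out mostly low hours. A worst-rank analysis of deaths can be added as an optional sensitivity analysis only.

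Give the SD for the chosen scale and the alpha used, and restate the ICP power. No revised power can be given here, because the documents contain no SD for a percentage of hours.

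The cost is wording in the protocol and analysis plan; the hourly readings are already collected. The downside is that the effect is expressed in percent rather than plain hours, and the stated power of 0.80 no longer applies as written.
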